### Sample size

Commonly, the sample size calculation is based on an expected incidence of the primary outcome. In our study, we have several primary outcomes regarding PIVC-related complications. Therefore, the sample size was calculated considering the lower prevalence value in Portuguese contexts for one of the primary outcomes (namely occlusion, with a 19% prevalence rate) [13, 28]. Also, the sample size determination was established using G*Power software, taking into consideration the type I (α) error level, the statistical power (type II error, β), and the standard deviation of the measurement for continuous outcomes. Fisher’s exact test comparing the proportions in two groups (*p* control = 0.19; *p* experimental = 0.05) are considered (Table 2). Ensuring a type I error of 5% and a statistical power of 80%, the estimated sample size is 146 participants (73 participants in each group).

**Table 2 Tab2:** Sample size estimation

Input		Output	
Tail(s)	One	Sample size group 1	73
Proportion p1	0.19	Sample size group 2	73
Proportion p2	0.05	Total sample size	146
α err prob	0.05	Actual α	0.0197
Power (1-β err prob)	0.80		
Allocation ratio N2/N1	1		

Fisher’s exact test: Proportions, inequality, two independent groups

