### Data collection, management, and analysis

Paper CRFs will be used in this clinical study to record all the information required from the protocol. Distinct CRFs will be used for the blinded and unblinded nurses. All CRF data are anonymized for subsequent analysis and reports/publications. According to this, study participants will be assigned a unique subject identification (ID) number. Study subject ID numbers will be used on all data collection instruments. The names of the participants on the consent forms will be stored separately from CRFs in locked cabinets and only accessible by named personnel.

Data to be collected include individual characteristics, demographics, and clinical information. No biological specimens will be collected. Data will be entered and analysed using the Statistical Package for the Social Sciences, version 24 (IBM SPSS Statistics 24, SPSS Inc., Chicago, IL, USA). Baseline characteristics of patients and catheters will be described by group. Means, standard deviations, frequencies, and percentages will be used as descriptive statistics. For each group, the number of participants who were randomly assigned will be analysed for the outcomes. Data analysis will be done using intention-to-treat principles [49]. Missing data will be handled using the last observation carried forward method, which uses the last available data for each trial participant, at the visit prior to withdrawal from the study, in the data analysis [50]. Specifically, for each primary and secondary outcome, the estimated effect size and its precision will be analysed. Baseline data for both groups will be observed to check for similarity in important variables. According to these results, variables with statistically significant differences between groups will be controlled in subsequent outcome analyses. The primary and secondary outcomes in the two groups will be examined to detect the effect of group allocation on each condition. Specifically, differences between continuous variables will be analysed using Student’s *t-*test. For skewed data, median values and interquartile ranges will be calculated and undergo nonparametric analysis using Mann-Whitney *U* test. Categorical variables will be compared by χ^2^ test or Fisher’s exact test, as appropriate. We deemed *p* values less than 0.05 to be significant (two-sided significance level of 5%). No additional analyses (e.g. interim analyses, planned subgroup analyses) will be performed.

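### The 146 patients and 80% power come from a one-tailed test, but the analysis is fixed as two-sided at 5%, where power is about 69% to 77% depending on the test

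*Protocol article*

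**What the plan says.** The Sample size section of the protocol article chooses occlusion as the outcome for sizing ("namely occlusion, with a 19% prevalence rate") and assumes that the new syringe lowers the rate to 5% ("experimental = 0.05"). It names the test as "Fisher’s exact test comparing the proportions in two groups" and concludes: "Ensuring a type I error of 5% and a statistical power of 80%, the estimated sample size is 146 participants", which is 73 per arm. Table 2 lists the software inputs: one tail, proportions 0.19 and 0.05, alpha 0.05, power 0.80, allocation ratio 1. Its outputs are 73 per group and an actual alpha of 0.0197.

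The section on data collection, management and analysis sets the rule for significance as a "two-sided significance level of 5" per cent, for p values in general and with no exception for occlusion. Categorical outcomes are to be compared by the chi-square "test or Fisher’s exact test, as appropriate".

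**The concern.** The sizing and the analysis describe different tests. A one-tailed test at 0.05 puts all of its error allowance on benefit from the new syringe. A two-sided test at 5% leaves about half of it there, so it rejects less often for the same data. The running text on sample size speaks only of a 5% type I error, and the one tail appears only in Table 2. Someone who reads the text together with the analysis section would take the 80% to be two-sided.

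Occlusion is the only outcome for which a sample size is given. If its power is lower than stated, a non-significant result would be weighed against a sensitivity that the trial does not have.

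**Working it through.** **Inputs.** Rates 0.19 (control) and 0.05 (double-chamber syringe), n = 73 per arm and one-tailed alpha 0.05 come from the Sample size section and Table 2. The two-sided 5% level and the choice of chi-square or Fisher's test come from the analysis section. No dropout allowance is stated, and none is applied.

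**Method.** Let X and Y be the numbers of patients with occlusion in the control and experimental arms. Exact power is the sum, over every table (x, y) that the test rejects, of

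Bin(x; 73, 0.19) × Bin(y; 73, 0.05).

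Exact size is the same sum with one common rate in both arms.

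**Step 1: reproduce the plan's figure.** One-sided Fisher p value ≤ 0.05:

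- n = 72: power 0.7944
- n = 73: power 0.8003
- size at a common rate of 0.05, n = 73: 0.0197

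Both 73 per arm and the actual alpha in Table 2 are recovered. The calculation really was one-tailed, and the entry in the table is not a misprint.

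**Step 2: same rates and n, two-sided 5%.**

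| Test | Power at 73 per arm | Chance of missing the effect |
|---|---|---|
| Fisher's exact | 0.691 | 0.309 |
| Chi-square, continuity-corrected | 0.691 | 0.309 |
| Pearson chi-square, uncorrected | 0.772 | 0.228 |
| Fisher if any expected count is below 5, otherwise uncorrected Pearson | 0.771 | 0.229 |

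The last row rests on a conventional reading of the words on choosing the test; the article does not state that rule. The mean expected number of events per arm is 73 × (0.19 + 0.05)/2 = 8.76. At the design rates an expected count falls below 5 in only about 1.3% of trials, so the rule almost always selects Pearson.

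Shortfall against 80.0%: 80.0 − 69.1 = 10.9 points at most, and 80.0 − 77.2 = 2.8 points at least.

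**Step 3: the n at which two-sided power reaches 80%, for scale.**

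- Uncorrected Pearson: 0.796 at 77 per arm, 0.802 at 78 (156 in total).
- Fisher: 0.803 at 90 per arm, 0.795 at 91, 0.8005 at 92, and above 0.80 from there to 104, the largest n checked. That is 180 to 184 in total.

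**Step 4: exact two-sided size at 73 per arm.**

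| Common rate | Fisher | Pearson, uncorrected |
|---|---|---|
| 0.05 | 1.44% | 4.84% |
| 0.08 | 2.26% | 5.26% |
| 0.10 | 2.63% | 5.12% |
| 0.12 | 2.83% | 5.00% |
| 0.19 | 2.94% | 5.04% |

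Pearson's advantage in power comes with a size that slightly exceeds 5% at some rates. If both arms had a rate near 5%, an expected count would fall below 5 in about 80% of trials.

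**The case against.** The strongest reply is that the shortfall may be small. A reader might infer that the trial's real power is simply 69% and its risk of a miss 31%, because Fisher's test is the one named for sizing. The analysis section does not support that, since it leaves chi-square open. On the conventional reading, chi-square would nearly always be used at the design rates, and power would then be about 77%. This point stands: 69% is the lower end of a range.

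A reader might also call this an arithmetic error or a concealed assumption. It is neither. The 146, the 80% and the 0.0197 are all correct for the one-tailed test, and Table 2, which the text cites, shows the tail openly. The fault is an inconsistency between two sections.

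It might further be thought that naming the Pearson chi-square would recover 8 points of power at no cost. That does not hold either: chi-square would probably be used anyway, and its exact size can rise a little above 5%.

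Finally, the plan promises an effect size and its precision for each outcome, which limits how far a null result could be over-read. That softens the consequence but does not correct the stated power. Nor is the contradiction a detail left to a fuller document, because both sides of it are printed in the article. If the one-tailed test were the intended one, the analysis section would be the passage to correct, so a reconciliation is needed in either case.

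**Conclusion.** The point holds as an inconsistency that makes the stated power wrong for the planned analysis. With 146 patients and a two-sided 5% level, power for occlusion is about 69% to 77% depending on the test, and the chance of missing the assumed effect is about 23% to 31%, not 20%. Every two-sided version of the permitted tests falls below 80%; only the size of the gap depends on which is used. The figures assume the plan's own rates of 0.19 and 0.05, 73 analysed patients in each arm, and no loss to follow-up.

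**What to change.** 1. Reconcile the sidedness of the Sample size section and Table 2 with that of the analysis section, and state it in the running text as well as in the table.
2. With the two-sided 5% level kept, restate the power at 146 patients: 69% with Fisher's exact test, 77% with the uncorrected Pearson chi-square.
3. Optionally, name one test for occlusion in advance, so that a single figure applies. If it is the uncorrected Pearson chi-square, note that its exact size reached about 5.3% at the rates checked and that it suits the data less well if both arms have rates near 5%.

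These are changes of wording and of Table 2. They need no extra patients; the cost is that the stated power becomes less favourable. If the sponsor prefers to keep 80% under a two-sided test, the totals are about 156 with the uncorrected Pearson chi-square or 180 to 184 with Fisher's test, before any allowance for dropout.

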### Data collection, management, and analysis

Paper CRFs will be used in this clinical study to record all the information required from the protocol. Distinct CRFs will be used for the blinded and unblinded nurses. All CRF data are anonymized for subsequent analysis and reports/publications. According to this, study participants will be assigned a unique subject identification (ID) number. Study subject ID numbers will be used on all data collection instruments. The names of the participants on the consent forms will be stored separately from CRFs in locked cabinets and only accessible by named personnel.

Data to be collected include individual characteristics, demographics, and clinical information. No biological specimens will be collected. Data will be entered and analysed using the Statistical Package for the Social Sciences, version 24 (IBM SPSS Statistics 24, SPSS Inc., Chicago, IL, USA). Baseline characteristics of patients and catheters will be described by group. Means, standard deviations, frequencies, and percentages will be used as descriptive statistics. For each group, the number of participants who were randomly assigned will be analysed for the outcomes. Data analysis will be done using intention-to-treat principles [49]. Missing data will be handled using the last observation carried forward method, which uses the last available data for each trial participant, at the visit prior to withdrawal from the study, in the data analysis [50]. Specifically, for each primary and secondary outcome, the estimated effect size and its precision will be analysed. Baseline data for both groups will be observed to check for similarity in important variables. According to these results, variables with statistically significant differences between groups will be controlled in subsequent outcome analyses. The primary and secondary outcomes in the two groups will be examined to detect the effect of group allocation on each condition. Specifically, differences between continuous variables will be analysed using Student’s *t-*test. For skewed data, median values and interquartile ranges will be calculated and undergo nonparametric analysis using Mann-Whitney *U* test. Categorical variables will be compared by χ^2^ test or Fisher’s exact test, as appropriate. We deemed *p* values less than 0.05 to be significant (two-sided significance level of 5%). No additional analyses (e.g. interim analyses, planned subgroup analyses) will be performed.

To ensure the efficiency and quality of the above procedures, a Steering Committee and Data Management team will be created, composed of the trial coordinator and the lead investigators from each collaborating centre. These teams will review and supervise ongoing trial tasks on a monthly basis, or whenever a non-expected event is reported. The representatives of the Data Management team in each collaborating centre will conduct weekly data checks in order to ensure the accuracy and quality of the information collected. Given the nature and duration of the trial, no Data Monitoring Committee will be created [51].

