Outcome assessment visits will be performed on a daily basis, in accordance with each participant’s period of prescribed intravenous drug administration. Using the same procedures in both groups (warranting the internal validity of the study), two distinct approaches will be considered (Table 1): (i) *unblinded visits* (always, at the time of the intravenous administration)—due to the nature of the interventions with the medical device, the wards nurses are aware of the participant allocation; (ii) *blinded visits* (once a day, outside the routine periods for drug administration by the ward nurses)—the research nurses are not aware of participant allocation and therefore there is no risk of distorting outcome measurements.

The *unblinded visits* will be performed by the ward nurses when the intravenous medications are administered (Table 1, type 4 visits). At this moment, the outcomes assessed will be phlebitis [47], infiltration [48], occlusion, catheter and insertion site analysis (main outcomes), as well as other reasons for catheter removal, maintenance time of the catheter, insertion attempts, and total number of catheters used (secondary outcomes; if applicable, i.e. when there is a need for new catheterization). The *blinded visits* will be performed by a research nurse who evaluates some of the main outcomes, namely phlebitis, infiltration, and catheter and insertion site analysis (Table 1, type 5 visits).

The last unblinded visit for outcome assessment will be performed at the end of the intravenous therapy by the ward nurse that removes the PIVC (Table 1, type 6 visits). During this visit, all the outcomes will be assessed by the ward nurses, with the exception of the insertion attempts and patient satisfaction. After the completion of the intravenous therapy and PIVC removal (Table 1, type 7 visits), research nurses will conduct a blinded visit similar to the previous type 5 visits. However, research nurses will also assess patients’ satisfaction about the clinical treatment. Finally, a follow-up assessment will be done (48–72 h after visit number 7) for the main outcome phlebitis (Table 1, visit 8). Throughout the study period, regardless of the type of visit, all adverse events will be assessed and recorded.

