### Outcomes

The main primary outcomes are the catheter-related complications, such as vascular trauma (phlebitis and infiltration) and occlusion. Specific scales for phlebitis [47] and infiltration [48] assessment will be used and data analysed in terms of mean scores, standard deviations, and proportions. The occlusion will be rated by the ward nurses on the participants’ case report forms (CRFs) and analysed as proportions.

The secondary outcomes involve other reasons for catheter removal (e.g. accidental dislodgment), maintenance time of the catheter, number of syringes and catheters used during the intravenous treatment, catheterization attempts, nurses’ perception about risk and safety, as well as the satisfaction of the participants. The reasons for catheter removal are reported on the CRF and treated as proportions. The maintenance time of the catheter, number of syringes and catheters used, and catheterization attempts are also identified on the CRF, being analysed through mean scores and standard deviations.

Ward nurses’ and patients’ satisfaction about the clinical treatment will be rated using questionnaires focused on essential risk and safety features, in a five-point Likert scale, developed and validated by the research team for this purpose. These scores will be analysed through mean scores and standard deviations.

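### Last observation carried forward scores participants who are event-free at their last visit as event-free thereafter, which lowers the primary complication proportions and understates their uncertainty

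*Protocol article*

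**What the plan says.** All of the following is in the protocol article.

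- **Missing data** (Data collection, management, and analysis): "Missing data will be handled using the last observation carried forward method", described as a method "which uses the last available data for each trial participant, at the visit prior to withdrawal from the study". No outcome is exempted and no other method is named.
- **Analysis set** (same section): "For each group, the number of participants who were randomly assigned will be analysed for the outcomes", under intention to treat. Carried-forward values therefore fill the denominator.
- **Further analyses** (same section): "No additional analyses (e.g. interim analyses, planned subgroup analyses) will be performed".
- **Primary outcomes** (Outcomes): phlebitis and infiltration are scored on scales, with "data analysed in terms of mean scores, standard deviations, and proportions". Occlusion is "rated by the ward nurses on the participants’ case report forms (CRFs) and analysed as proportions".
- **Observation period** (Interventions): assessments are daily, "in accordance with each participant’s period of prescribed intravenous drug administration", so its length differs between participants. One further assessment, 48–72 h after visit 7, is made "for the main outcome phlebitis (Table 1, visit 8").
- **Dropout** (Sample size): no rate is stated, and the 146 contains no allowance for it.

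**The concern.** Carry-forward assumes that a participant's status stops changing once observation stops. A complication of an indwelling catheter does not behave like that, because a participant who is free of occlusion on day 2 can still have one on day 4. If that participant withdraws on day 2, the rule enters a definite non-event for the whole course. The error in each proportion runs one way: events that would have occurred after leaving are lost and none are added.

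Visit 8 is a special case for phlebitis. It exists to look for phlebitis after the catheter is out. Filling it from visit 7 assumes that nothing new appeared in the interval that the visit was set up to observe.

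Two things are at stake. The complication rates reported for a new device would be too low in any arm with early leavers. The confidence intervals would also rest on 73 apparently complete observations per arm when some are guesses. The comparison between arms is affected too, but in a way that depends on who leaves each arm and when.

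**Working it through.** **1. The plan's own figure.** Sample size section and Table 2: 0.19 control, 0.05 experimental, one-sided Fisher's exact test, α = 0.05, power 0.80, 73 per arm. Enumerating all 2×2 tables gives power 0.794 at 72 per arm and 0.800 at 73. The actual α at a common proportion of 0.05 is 0.0197. The stated 146 is reproduced. It does not depend on the missing-data rule.

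**2. Model for carry-forward.** Let p be the true proportion, d the share of an arm that leaves early, and f the share of leavers' events that would occur after they leave. Leavers are taken to have the same underlying risk as the others. Events recorded before leaving are kept, so

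observed proportion = p × (1 − d × f).

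p comes from the Sample size section (occlusion). d and f are assumptions, since the document gives neither.

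**3. Equal dropout in both arms.**

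| d | f | Control | Arm A | Difference | Risk ratio | One-sided Fisher power |
|---|---|---|---|---|---|---|
| 0 | – | 0.190 | 0.050 | 0.140 | 0.263 | 0.800 |
| 10% | 0.5 | 0.1805 | 0.0475 | 0.133 | 0.263 | 0.777 |
| 20% | 0.5 | 0.171 | 0.045 | 0.126 | 0.263 | 0.752 |
| 20% | 1 | 0.152 | 0.040 | 0.112 | 0.263 | 0.693 |

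The factor (1 − d × f) is common to both arms, so it cancels in the risk ratio and shrinks the difference.

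**4. Unequal dropout, f = 0.5, planned effect true.**

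- 20% control, 5% arm A: 0.19 × (1 − 0.20 × 0.5) − 0.05 × (1 − 0.05 × 0.5) = 0.171 − 0.04875 = 0.122.
- 5% control, 20% arm A: 0.19 × (1 − 0.05 × 0.5) − 0.05 × (1 − 0.20 × 0.5) = 0.18525 − 0.045 = 0.140. The risk ratio becomes 0.045 / 0.18525 = 0.243 instead of 0.263.

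**5. Unequal dropout, no true effect (0.19 in both arms).** With 5% against 20%:

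- f = 0.5: 0.19 × 0.975 − 0.19 × 0.90 = 0.014.
- f = 1: 0.19 × 0.95 − 0.19 × 0.80 = 0.0285.

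The arm with more leavers looks better by 1.4 to 2.9 points. Two-sided Fisher rejection at 73 per arm rises from 0.029 to between 0.033 and 0.046. In the extreme case of 0% against 20% with f = 1 it reaches 0.060.

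**6. Precision.** The standard error of the difference, computed on 73 per arm with carried-forward values (f = 0.5), is compared with the standard error from 73 × (1 − d) fully observed participants per arm at the true rates:

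- d = 5%: 0.0520 / 0.0539 = 0.96
- d = 10%: 0.0514 / 0.0554 = 0.93
- d = 20%: 0.0503 / 0.0587 = 0.86

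The comparator ignores what leavers contribute before leaving, so these ratios somewhat exaggerate the understatement. The direction is clear.

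**7. Visit 8.** The stated rule speaks of the visit before withdrawal. It does not say in terms what happens when only visit 8 is missing. If the rule is applied there, a participant without phlebitis at visit 7 is entered as without phlebitis at visit 8. The document gives no phlebitis rate or visit 8 attendance, so no size is offered.

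**The case against.** The strongest reply is that the effect may be small. Follow-up covers only the prescribed therapy plus a few days, withdrawal may be rare, and equal dropout leaves the risk ratio alone. With no true effect, 5% against 20% dropout keeps two-sided rejection below 5%, because Fisher's test is conservative at this size. All of this stands, and it limits the claim about the comparison. It does not rescue the rule, which still lowers each proportion and counts guesses as data.

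Four stronger readings are tempting, and the document does not support them.

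- *Everyone who leaves early is counted as event-free.* A participant with a complication at the last visit keeps it. Only those event-free at that visit are affected, and visit 8 bears on phlebitis alone.
- *Two hidden events overturn the trial.* At about the planned rates, 14/73 against 4/73 gives a two-sided Fisher p of 0.021, and 14 against 6 gives 0.090. That hides events in arm A only; two in each arm gives 16 against 6, p = 0.036. If leaving is unrelated to outcome, hiding 2 of 6 events needs d × f = 1/3, that is, a third of arm A leaving before any risk or two thirds leaving halfway.
- *Carry-forward replaces an earlier phlebitis with the score of a newly sited catheter.* Nothing says that the last score is the one analysed. If it were, participants with complete follow-up would have the same problem. That is a question of outcome definition.
- *A missing-data sensitivity analysis is ruled out.* The sentence excluding additional analyses gives interim and subgroup analyses as its examples, and an analysis plan not shown may add more. The point here is the method that is fixed.

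The alternatives also carry assumptions. Censoring at the last assessment requires non-informative censoring, and multiple imputation with about four expected events in an arm (73 × 0.05 = 3.65) is not robust. This is why the sensitivity analysis belongs in the fix.

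**Conclusion.** The point holds in limited form. As written, the rule counts participants who are event-free at their last visit as event-free thereafter, biases complication proportions downward, and understates uncertainty. That follows from the rule and the nature of the outcomes, provided some event-free participants leave before the end of therapy and some of them would have had a later event.

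The size cannot be fixed from the document. With equal dropout of 10% to 20% and f from 0.5 to 1, the planned 14.0-point difference falls to between 13.3 and 11.2 points. With unequal dropout the difference may shrink (12.2 points) or stay at 14.0, depending on which arm loses more. A reader might infer a known bias for or against the new syringe. Patients and ward nurses are not fully blinded, so arm-dependent withdrawal is possible, but nothing in the document shows that it will happen or in which direction.

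The change is worth making before data are analysed. It does not invalidate the design.

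**What to change.** Replace the carry-forward sentence with wording to this effect:

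1. A participant has a primary event if it is recorded at any scheduled assessment.
2. For a participant without an event whose follow-up is incomplete, the outcome is missing. For phlebitis this includes an unobserved visit 8.
3. These outcomes are handled either by multiple imputation, using arm, hospital and baseline variables, or by cumulative incidence per arm with censoring at the last assessment. One of the two is named in advance.
4. A simple sensitivity analysis varies the assumed event rate among these participants separately by arm and shows where the conclusion would change.

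**Cost.** Protocol or analysis-plan wording and slightly more programming, with somewhat wider intervals. The main analysis will rest on a missing-at-random or non-informative censoring assumption, which item 4 tests. The article says that catheter insertion date and time are collected and that visits are daily. It does not say that the case report form holds the date of each assessment, so this should be confirmed before censoring is chosen.

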### Randomization, concealment, and group allocation procedures

The participants will be randomised after meeting two eligibility criteria screenings (Table1). Eligible and consenting participants will be randomly assigned to one of two treatment groups (arm A, double-chamber syringe; arm B, traditional syringes) using simple randomization with a 1:1 ratio. In each participating hospital ward nurses will have access to a central randomization and online registration system (https://www.sealedenvelope.com/). Before patient inclusion in the study, ward nurses will log into the online system and provide the participant’s anonymous ID number. The central system will randomly allocate the participant to one of the two groups and inform the nurse in real time. All allocations will be recorded into the central system and can only be accessed by the study’s principal investigator, ensuring allocation concealment across sites.

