The rigorous eligibility criteria will ensure the control of important variables that could impact on the trial’s results. For example, catheter size and insertion site are important factors for catheter longevity. Although the use of larger diameter catheters significantly increases catheter longevity [58] and reduces the risk of accidental removals [15], larger sizes also predict the incidence of phlebitis and subsequent catheter failure [15, 59]. In light of the contradictory results from several studies about catheter size, we defined the use of 18 or 20 gauge catheters, which are the most used in the orthopaedic departments that will participate in the clinical study. Regarding the anatomical insertion site, it is well accepted that upper extremity veins are desirable for patient comfort and fewer complications [16, 17, 19, 37]. Also, several studies have shown that catheter placement in the forearm significantly increased their longevity [15, 16, 37, 58]. Catheters in the cubital fossa region have been associated with higher incidence of complications such as phlebitis or occlusion [15, 16, 37, 59]. Similarly, anatomical areas of flexion must be avoided due to the high risk of complications such as dislodgement and phlebitis [17]. According to the existing evidence, this trial will only include patients with a PIVC inserted in their arm, forearm, or back of the hand.

Despite the strengths of this protocol, some limitations should be pointed out, such as the impossibility to perform a totally blinded assessment for all the outcomes. In fact, only a select number of outcomes will be assessed by the blinded research nurses (e.g. phlebitis), given that the majority of the outlined outcomes can only be assessed at the exact moment of intravenous administration with the double-chamber or traditional syringes. Moreover, the study will be implemented within a specific context (orthopaedics departments), which may condition a broader analysis of the results obtained. To address this challenge, future studies should be done in other clinical contexts that involve intravenous therapy administration.

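### Adjustment covariates are to be picked by baseline significance tests, so chance rather than prognostic value decides the outcome analysis

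*Protocol article*

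**What the plan says.** All references are to the protocol article.

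- **Data collection, management, and analysis.** "Baseline data for both groups will be observed to check for similarity in important variables". Next comes the rule: "variables with statistically significant differences between groups will be controlled in subsequent outcome analyses". The variables that count as important are neither listed nor counted.
- **Same section, outcome tests.** Student's t and Mann-Whitney are named for continuous outcomes. "Categorical variables will be compared by" the chi-square "test or Fisher’s exact test, as appropriate". The level is given as a "two-sided significance level of 5" per cent.
- **Randomization, concealment, and group allocation procedures.** Participants are allocated centrally, "using simple randomization with a 1:1 ratio". No stratification is stated.
- **Discussion.** The authors write that "catheter size and insertion site are important factors for catheter longevity" and report studies in which "catheter placement in the forearm significantly increased their longevity". They also describe the evidence on catheter size as contradictory, and they handle both factors through eligibility.
- **Participant recruitment and eligibility criteria.** Two gauges (18G and 20G) and three upper-limb sites remain admissible.

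Nothing elsewhere in the article fixes a covariate set or withdraws the rule.

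**The concern.** With sound central randomisation, any baseline difference between the arms is a chance difference. Its p-value therefore says nothing about whether the variable predicts occlusion, phlebitis or infiltration, and that is the only property that makes adjustment worthwhile. The rule can admit an irrelevant variable that happens to cross 0.05, and it omits a strong predictor whose imbalance falls short of significance.

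Two things are at stake. The analysis of every primary and secondary outcome depends on how the baseline table turns out. And whatever precision could be gained from prognostic factors is mostly given up, because they enter only by luck.

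This is a stated rule, not a detail left for later. An analysis plan could not follow that sentence and also fix its covariates in advance.

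**Working it through.** **The plan's own figure.** Table 2 gives 73 per arm for a one-tailed Fisher test of 0.19 versus 0.05. Full enumeration gives power 0.8003 at 73 per arm and 0.7944 at 72. The actual alpha with both rates at 0.05 is 0.0197. The stated 146 and 0.0197 are reproduced. (One tail in Table 2 against two-sided testing in the analysis section is a separate matter.)

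**Chance that the rule is triggered by luck.** The inputs are a 5% level, assumed to apply to the baseline tests too, and k independent tests. The Interventions section names roughly a dozen items as examples, so k is taken from 5 to 20. The formula is 1 − 0.95^k.

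| k | Chance that at least one is selected | Expected number selected |
|---|---|---|
| 5 | 23% | 0.25 |
| 10 | 40% | 0.50 |
| 12 | 46% | 0.60 |
| 20 | 64% | 1.00 |

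Any one factor, prognostic or not, is left out with probability 1 − 0.05 = 95%.

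**Imbalance that the rule lets pass.** At 73 per arm a binary factor of prevalence p must differ by about 1.96 × √(2p(1 − p)/73):

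- p = 0.5: 1.96 × √(0.50/73) = 0.162, about 16 percentage points.
- p = 0.3: 1.96 × √(0.42/73) = 0.149, about 15 percentage points.

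Smaller imbalances go unadjusted, however prognostic the factor.

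**Effect on error rate and power.** A simulation used 40,000 runs, 73 per arm, two-sided 5% tests, one continuous covariate, and an effect of 0.465 SD, which gives about 80% unadjusted power. The covariate–outcome correlations are assumed.

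| Correlation | Type I: unadjusted | Type I: baseline-test rule | Type I: always adjusted | Power: unadjusted | Power: baseline-test rule | Power: always adjusted |
|---|---|---|---|---|---|---|
| 0.3 | 0.049 | 0.046 | 0.049 | 0.80 | 0.80 | 0.83 |
| 0.5 | 0.049 | 0.042 | 0.048 | 0.80 | 0.81 | 0.89 |
| 0.7 | 0.051 | 0.036 | 0.049 | 0.80 | 0.82 | 0.97 |

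The rule performs almost like no adjustment and captures little of the available gain. Its error rate lies below 5%, not above it.

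**Events available for a model.** At the design rates, 73 × 0.19 + 73 × 0.05 = 13.87 + 3.65 = 17.5 occlusions are expected. With 19% in both arms, 146 × 0.19 = 27.7. So about 17.5 to 28 occlusions must support the model.

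**The case against.** The strongest defence is that randomisation keeps the unadjusted comparison valid whatever the chance imbalance, so the rule costs efficiency and clarity rather than validity. That stands, and it limits how serious the point is. Several stronger readings are tempting, but the article does not support them.

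- **Inflated false positives.** A reader might infer that a data-dependent analysis raises the type I error. The simulation shows the opposite for this rule alone, 0.046 to 0.036. It does not measure any freedom to choose the adjusted model afterwards, so inflation is unproven rather than excluded.
- **The analysis changes in about half of such trials.** The 46% needs 12 independent tests. Only variables deemed important are checked, and some collected items are doubtful candidates: dressing type is fixed by eligibility, and drugs injected may follow randomisation. Positively correlated variables would usually lower the figure. Only the range can be defended.
- **Known predictors of occlusion are being discarded.** Hospital is never named as prognostic. The one site that the Discussion links to occlusion, the cubital fossa, is excluded. Among permitted sites it reports only longer survival in the forearm. Its gauge evidence concerns longevity, accidental removal, phlebitis and catheter failure, and is called contradictory. Eligibility narrows both factors.
- **The adjusted analysis has no method.** The listed tests take no covariate, but an article may leave the model to the full protocol or analysis plan. This is not a finding in itself.
- **Too few events for any adjustment.** The 17.5 occlusions assume the full design effect. Occlusion was chosen as the primary outcome with the lowest prevalence, and mean scores do not raise this problem.

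None of this rescues selection by p-value.

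**Conclusion.** The point holds as a badly fixed selection rule that should be changed. About 5% of variables would be selected regardless of prognostic value, and a prognostic factor would be missed about 95% of the time. Some chance-driven adjustment would occur in 23% to 64% of trials with 5 to 20 tests. These figures assume independent tests at the 5% level, and the number of tests is not in the article.

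The consequences are a data-dependent primary analysis, a somewhat conservative test, and lost precision relative to fixed adjustment. In the simulation the power forgone against fixed adjustment was about 3, 9 and 16 percentage points at correlations of 0.3, 0.5 and 0.7. Those correlations are assumptions. If gauge and site prove only weakly prognostic within the permitted ranges, the loss is small. The case for change then rests on having the analysis fixed in advance.

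**What to change.** 1. Delete the sentence that ties adjustment to baseline significance. Report baseline data descriptively, without p-values.
2. Fix one primary analysis per outcome type, with the same short covariate set used regardless of balance:
   - **Binary outcomes** (occlusion; phlebitis and infiltration as proportions): Firth logistic regression on arm, catheter gauge (18G/20G) and insertion site of the first catheter (forearm versus other).
   - **Phlebitis and infiltration mean scores:** a linear model on arm and the same two covariates.

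The set is kept to two covariate parameters on purpose. With arm, that is three parameters for 17.5 to 28 occlusions, or about 5.8 to 9.2 events each (17.5/3 and 27.7/3). Adding hospital (two parameters) and keeping three site levels (two) would make six parameters with arm and gauge, or about 2.9 events each (17.5/6).

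Both covariates are already collected (Interventions). They should be those of the first catheter, because later catheters follow randomisation. Both are eligibility conditions, so they should be known before allocation; the sponsor should confirm this against the assessment schedule.

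The cost is a few sentences of text and a little more analysis work, with no change to the sample size of 146. The odds ratio becomes conditional on the two factors and should be reported as such. Precision gains little if the factors turn out weakly prognostic.
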